**Methods:**

In this pilot study we will utilize a double-blind, randomized, placebo-controlled design. Inclusion criteria will include adult patients with severe CTS. This will be confirmed by nerve conduction studies and motor unit number estimation (MUNE). Only those with severe motor unit loss in the thenar muscles (2 standard deviations [SD] below the mean for the age group) will be included. Eligible patients will be randomized to receive 3,000 mg/day of ALCAR orally or placebo following carpal tunnel release surgery for 2 months. The primary outcome will be MUNE with supplementary secondary outcome measures that include: 1) two-point discrimination; 2) Semmes-Weinstein monofilaments for pressure sensitivity; 3) cold and pain threshold for small fiber function; 4) Boston self-assessment Carpal Tunnel Questionnaire and 5) Disabilities of the Arm, Shoulder and Hand (DASH) questionnaire for symptom severity; and 6) Purdue Pegboard Test for hand functional performance. To follow post treatment recovery and monitor safety, patients will be seen at 3 months, 6 months and 1 year. The outcome measures will be analyzed using two-way ANOVA, with treatment assignment and time points being the independent factors. If significant associations are detected, a post hoc analysis will be completed. We aim to recruit ten patients into each of the two groups. Data from this pilot will provide the basis for power calculation for a full-scale trial.

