### Primary outcome

The primary endpoint will be motor axon reinnervation in the thenar muscles. This will be done using MUNE, a non-invasive electrophysiological technique. Initially introduced in the 1970s [19, 20], multipoint stimulation, the most commonly used MUNE technique, has been shown to be a reliable test for measuring motor axon reinnervation [5]. Apart from providing an objective assessment of large myelinated nerve fibers, MUNE will also serve as a screening tool for eligibility for the trial. To quantify treatment response, MUNE will be repeated at 3, 6 and 12 months post-operatively.

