### Secondary outcomes

Secondary outcomes of the study focus on sensory function restoration and functional outcomes. Measures will include:Two-point discrimination (Aβ fibers) using Dellon-MacKinnon DiskPressure sensitivity (Aβ fibers) using Semmes-Weinstein monofilamentCold threshold (Aδ fibers) and pain threshold (C fibers) using CASE IV quantitative sensory testing (QST) equipmentBoston CTS Questionnaire to monitor symptom severityDisabilities of the Arm, Shoulder and Hand (DASH) questionnaire for functional outcomesMoberg Pick-up Test to measure hand dexterity and functional performance

All outcome measures will be monitored at baseline, 3 months, 6 months and 12 months. Sensory testing of peripheral nerves provides more of a challenge, given the multiple fiber types that provide sensory feedback. The above list of tests is designed to capture the full range of sensory fiber functions. A major advantage of QST is that it provides an objective means of measuring the function of different classes of nerve fibers with good reliability. The DASH and the Boston questionnaires used to evaluate symptom severity are both well validated in CTS [21]. Finally, to objectively measure hand functional performance, the Moberg Pick-up Test is a validated tool for CTS with good reliability [22]. All primary and secondary outcome measures will be performed by the same investigators (MC, KMC). To verify the inter-rater reliability of these tests, a subset of patients will undergo separate assessment by two investigators independently in a blinded manner.

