### Sample size

Initially, a pilot study of 20 patients will be carried out. Evaluation of the effect size will be based on the primary outcome MUNE. This will provide the necessary data for the sample size calculation for a fully powered large-scale study.

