### Statistical analysis

Demographic data will be compiled and analyzed for differences using a Student’s *t*-test and Fisher’s exact test. The primary and secondary outcome measures will be analyzed using two-way ANOVA with the treatment groups and time points being the independent factors. If significant associations are detected, a post hoc analysis will be done for pairwise comparisons. Due to the exploratory nature of the study, sample size calculations and formal analysis of missing data will not be undertaken.

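### The analysis section rules out formal missing-data analysis without saying how incomplete patients enter the four-visit ANOVA whose MUNE results are to size the full trial

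*Protocol article*

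**What the plan says.** In the protocol article, Statistical analysis fixes the model: "The primary and secondary outcome measures will be analyzed using two-way ANOVA with the treatment groups and time points being the independent factors". The same paragraph then excludes work on missing data and gives its reason: "Due to the exploratory nature of the study, sample size calculations and formal analysis of missing data will not be undertaken".

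The visit schedule is under Secondary outcomes: "All outcome measures will be monitored at baseline, 3 months, 6 months and 12 months". For the primary outcome, the Primary outcome section says that "MUNE will be repeated at 3, 6 and 12 months post-operatively", and that MUNE also screens for eligibility.

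On size and purpose, the Sample size section says: "Initially, a pilot study of 20 patients will be carried out". The abstract splits this evenly: "We aim to recruit ten patients into each of the two groups". The Sample size section continues: "Evaluation of the effect size will be based on the primary outcome MUNE", and "This will provide the necessary data for the sample size calculation for a fully powered large-scale study".

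The article does not say whether the ANOVA is of the repeated-measures kind, whether a patient with a missed visit is kept or removed, or how many losses are expected.

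**The concern.** A condensed article may leave much of its missing-data plan to a fuller document. Here, however, the article takes a position: formal analysis of missing data is excluded because the study is exploratory. An analysis plan that added such an analysis would depart from the published text.

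The position sits badly with the rest of the paragraph. Follow-up runs to 12 months with three visits after surgery, so some missed visits are likely. The two usual readings of the stated ANOVA treat incomplete patients quite differently, and neither treats them well. With ten patients per arm, each loss weighs more than it would in a large trial.

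What is at stake is mainly the pilot's declared product. The MUNE effect size, and the SD that must accompany it in any sample size calculation, go straight into the design of the full trial. If loss is related to recovery, both can be distorted, and nothing in the stated plan would show it.

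**Working it through.** **Inputs from the article.** 20 patients, 10 per arm; four visits, of which three are follow-up visits. MUNE is an entry criterion, so baseline MUNE should be complete and only the three follow-up visits can be missed. The article gives no missingness rate, alpha, power, effect size or SD. The figure of 20 has no calculation behind it to reproduce. All missingness rates below are assumptions.

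**Reading 1: classical repeated-measures ANOVA.** A patient missing any visit is removed.

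- If each follow-up visit is missed independently with probability m, the expected number of complete patients is 20 × (1 − m)³.

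| m | (1 − m)³ | Complete patients of 20 |
|---|---|---|
| 5% | 0.857 | 17.1 |
| 10% | 0.729 | 14.6 |
| 15% | 0.614 | 12.3 |
| 20% | 0.512 | 10.2 |

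- If patients leave and do not return, with total dropout d, the number is 20 × (1 − d): 18 at d = 10% and 16 at d = 20%. This is the milder pattern.
- In patient-visits, at m = 10% listwise deletion keeps 80 × 0.729 = 58.3 of 80. Using every available visit keeps 20 + 60 × 0.90 = 74.
- The detectable standardised difference at a single time point (two-sided 5%, 80% power, normal approximation) is (1.96 + 0.84) × √(2/n). It is 1.25 SD at n = 10 per arm, 1.32 at 9, 1.40 at 8 and 1.50 at 7. Power for a 1 SD effect falls from 61% at 10 per arm to 56%, 52% and 46%.

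**Reading 2: ordinary two-way ANOVA.** No patient is removed, so the counts above do not apply. Two other problems arise.

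- Up to four measurements on one patient are treated as four independent observations.
- Each arm-by-visit mean is the mean of whoever attended. Suppose a fraction f of one arm is absent at a visit, and those absent would have averaged δ below those present. The observed mean then exceeds the full-arm mean by f × δ. With 2 of 10 absent, the shift is 0.2δ. If the other arm is unaffected, the whole shift enters the between-arm difference. If both arms lose patients in the same way, it largely cancels from the difference, though the SD can still be affected.

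**Attrition as a pilot result.** It needs only a count out of 20. Exact (Clopper–Pearson) 95% intervals are 1.2% to 31.7% for 2/20 and 5.7% to 43.7% for 4/20. For a notional full trial needing 100 evaluable patients, N = 100/(1 − attrition), rounded up. This gives 112 at 2/20 (102 to 147 across the interval) and 125 at 4/20 (107 to 178).

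**The case against.** The strongest reply has four parts.

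*The article never says that incomplete patients will be dropped.* This is right. It names neither a repeated-measures form nor a deletion rule, and under the most literal reading the rows are kept. A reader might infer that a complete-case analysis is planned; the text does not support that. The counts of 17, 15, 12 and 10 hold only under Reading 1 with independent missingness, and the dropout pattern gives milder figures.

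*Losses can still be counted.* This is also right. A reader might infer that excluding formal missing-data analysis leaves the pilot unable to supply an attrition rate. No section says dropouts will go uncounted or unreported. The article does not name attrition as a pilot output, and the real limit is precision at 20 patients.

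*The excluded formal analysis may mean only imputation or sensitivity analysis.* This is possible, and a mixed model could then be run beside the sentence as it stands. But the article names a two-way ANOVA, not a mixed model, so the treatment of incomplete patients stays open on that reading too.

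*The study is exploratory, and Limitations admits low power.* This lowers the consequences but does not answer the point. The Objective section is about efficacy, the MUNE result is meant to size the next trial, and Limitations does not mention missing data. The article also describes the drug as well tolerated and limits dosing to 2 months, which makes loss from intolerance less likely. Loss related to recovery over the remaining months is still possible.

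**Conclusion.** The point holds in this form: the article excludes formal analysis of missing data and sets a four-visit ANOVA with no stated treatment of incomplete patients. Either usual form of that ANOVA has a cost. The repeated-measures form loses patients: about 15 of 20 kept at 10% independent missingness per follow-up visit, or 18 of 20 at 10% total dropout. The ordinary form ignores within-patient correlation and lets the patient mix shift between visits. Selective loss can then distort the MUNE effect size and SD carried into the full trial.

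The size rests on assumed rates and on which ANOVA is meant. Bias is conditional: it arises only if loss is related to outcome, and in the between-arm difference mainly if that relation or the amount of loss differs between arms. For a pilot that admits its low power this is a weakness worth correcting; it does not invalidate the design.

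**What to change.** In Statistical analysis, replace the two-way ANOVA and the exclusion of missing-data analysis with a likelihood-based mixed model for repeated measures. It should include all randomised patients in their assigned arm and every available visit, with treatment, visit and their interaction as fixed effects and within-patient correlation modelled. State that it is valid under missing at random and does not remove bias from loss that depends on unobserved outcomes.

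Add a table of missed visits by arm, visit and reason. Carry the observed attrition, with its interval, into the full-trial calculation alongside the MUNE difference and SD.

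The cost is a change of wording, slightly more analysis work and one table. No extra patients, visits or measurements are needed. The downside is reliance on the missing-at-random assumption, which 20 patients cannot test.

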### Safety and potential risks

To monitor any potential adverse events, rigorous safety measures have been put in place to ensure patient safety. Initial baseline testing will include:Physical examinationVitalsEKGUrine pregnancy testsComplete blood count with differential, electrolytes (Na, K, Cl, CO_2_), creatinine, urea, alanine aminotransferase, aspartate aminotransferase, alkaline phosphatase and bilirubinSerum ALCAR

Vital signs (blood pressure, temperature, pulse, respiratory rate, oxygen saturation) will be recorded at every visit. Safety lab tests including blood chemistries will be done at screening, and periodically during follow-up visits. In addition, an electrocardiogram will be done at screening. The serum ALCAR level will also be monitored. In healthy subjects, the serum ALCAR levels had a range of 10–70 μmol/L with a mean of 39 μmol/L. In a large study of over 333 patients with diabetic neuropathy taking 3 g of ALCAR/day (the same dose used in this study), the rise in serum level was only around 50 % compared to baseline. Since no sign of ALCAR toxicity was observed in any of the subjects, we anticipate that the chances of toxic effects in this study will be very small.

All adverse events will be documented at follow-up visits. Further laboratory investigations will be done depending on the nature and severity of the adverse events reported.

### Trial management

The trial will be managed by a trial steering committee in accordance with Good Clinical Practice guidelines. The principle investigator, [name] (KMC), will be primarily responsible for the overall trial functioning with assistance from [name] (MC). The administration of the study drug will be completed through the Research Pharmacy Office located at the Kaye Edmonton Clinic. Adverse events will be tracked and managed by a Drug Safety Monitoring Board. The trial has been registered with Clinicaltrials.gov (CT02141035)*.*

### Ethics

The study has ethical approval from the Health Research Ethics Board (Pro00045538) at the University of Alberta. The trial will be conducted in keeping with the principles of Good Clinical Practice.

## Discussion

Acetyl-L-carnitine is a peptide natural product that plays a crucial role in fatty acid metabolism, acyl group transfer and transport into mitochondria. It has been shown to be beneficial in a number of disease states including oligospermia [24], hepatic encephalopathy [25] and dysthymia [26]. It has also been shown to have a positive impact on central and peripheral nervous system diseases. It can reverse signs of aging in rat brains [27]. In peripheral neuropathies it is thought that ALCAR enhances nerve growth factor receptor binding, allowing for neurite outgrowth through the ERK pathway [13, 28]. This effect has been demonstrated in diabetic neuropathy [15], chemotherapy-induced peripheral neuropathy [16] and antiretroviral toxic neuropathy [14]. ALCAR is very well tolerated. Large trials have shown minimal side effects. Its practicality is further enhanced by the fact that the drug is active in oral preparation.

### Strengths

Vigorous measures have been built into the study design. To prevent potential bias, we utilize a double-blinded, placebo-controlled design. To further reinforce this, data entry and review will be handled by a monitoring committee that will be working at arm’s length from the investigators who are directly interacting with the study subjects. Surgery will be performed by two experienced surgeons using a standardized technique for carpal tunnel release. To measure the effects of the therapeutic agent on nerve regeneration, we will be using MUNE as the primary outcome measure. This provides a physiological measure that can be directly compared with the data from animal studies. In addition, the protocol will also incorporate tests to provide comprehensive information on the full range of sensory nerve fibers.

### Limitations

A potential limitation of our study is generalizability of the results. Since we will be deliberately focusing on only CTS patients with severe motor axonal loss, the results may not be applicable to those with mild and moderate disease. However, since severe carpal tunnel patients have the lowest potential for recovery even with surgery, it would be important to target this population. A second limitation of the study is that it is likely underpowered. However, since no prior studies on the effect size and variability of ALCAR in compressive neuropathy are available, data from this pilot study will be very useful in designing a full-scale study. The multiple comparisons would also reduce the statistical power of the study. Since this is meant to serve as an exploratory study, these considerations are not of primary concern.

Here we present a phase II randomized control trial design to determine the role of ALCAR in peripheral nerve regeneration in CTS. This is the first human study that looks at the efficacy of ALCAR in patients with compressive neuropathy. If effective, ALCAR will represent an important adjuvant therapy for patients with CTS. By improving motor and sensory recovery, patients could potentially return to their work and daily routines more quickly.

### Trial status

Currently recruiting NCT02141035.

## Abbreviations

ALCAR: acetyl-L-carnitine
ANOVA: analysis of variance
CTS: carpal tunnel syndrome
EMG: electromyography
JO: [name]
KMC: [name]
MC: [name]
MM: [name]
NOL: No Objection Letter
MUNE: motor unit number estimation
QST: quantitative sensory testing
SC: Schwann cell
SD: standard deviation
